## **6.2. Study Duration and Visit Schedule**

Enrollment through follow-up is estimated to require 18 months. The study continues until MTD has been determined or the upper dose limit of this protocol has been reached without determining the MTD. The dose-level cohort that represents the RDL will be expanded to 6 subjects to confirm the RDL.

All study assessments by visit are defined in the [Table 3](#) and safety assessments in Section 11.

### **6.2.1. Screening**

A two-tiered screening will be conducted in the one-month period prior to dosing. The first tier is designated the pre-run-in screening ([Table 3](#)) and will take place one month prior to dosing. At this screening, the subject will be guided through the informed consent process and a preliminary evaluation of suitability for the study, including a medical history and a blood draw for assessment of peripheral iNKT cell numbers. It is important to note that if a subject does not have measurable peripheral iNKT cell numbers, he/she cannot participate in the trial.

If a subject meets the criteria defined in the first tier of screening, the subject will take part in the second tier of screening two-weeks prior to dosing ([Table 3](#)). If the subject meets the criteria defined in the second tier of screening, the subject will be instructed in the use of the eDiary and scheduled for dosing in two weeks.

---

Note that due to the schedule of events, subjects may only be dosed on Mondays or Tuesdays so that all subsequent, in-clinic evaluations may occur Monday through Friday.

### **6.2.2. Treatment and follow-up**

Treatment consists of a single IV dose of NKTT120 administered slowly over ten (10) minutes. Each subject will be followed until one month after iNKT cells have recovered to detectable levels. Total duration of follow-up post-dosing will vary based on the dose level received. Currently it is anticipated that iNKT cells will return to detectable levels within 1 month after NKTT120 is no longer detectable in the serum; in the lower dose cohorts; at the highest dose (0.1 mg/kg) this could be  $\geq 6$  months based on preliminary PK in non-human primate).

## **6.3. Study Endpoints**

### **6.3.1. Primary Endpoint**

The primary endpoint is the MTD or RDL. The MTD is determined by a cohort in which 2 of 6 subjects experience a DLT. The study continues until MTD has been determined, or until the upper dose limit of this protocol has been reached without reaching the MTD. The dose-level cohort that represents the MTD will be expanded to 6 subjects to confirm MTD.

If the highest dose level is reached without determining a MTD, the RDL(s) for phase 2 will be determined by a dose that is at or below the highest dose and which is associated with iNKT cell recovery that allows dosing every 4-6 months in phase 2 studies.

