#### **Statistical methods:**

Primary outcome: Maximum tolerated dose (MTD) is defined as the dose level that is estimated to produce DLT in < 33% of subjects in a cohort using a 3+3 design. If no MTD is achieved, the RDL will be determined based on the overall safety profile of NKTT120 and the duration of iNKT cell depletion.

Secondary outcome: Non-compartmental pharmacokinetic parameters--peak concentration ( $C_{max}$ ), minimum concentration ( $C_{min}$ ), average concentration ( $C_{avg}$ ), area under the time-concentration curve (AUC), half-life ( $t_{1/2}$ ), volume of distribution ( $V_d$ )--will be calculated for all subjects. Descriptive statistics of these parameters will be provided by dose level.

Descriptive statistics of the PK/PD (peripheral iNKT cell subset/T cell (TC) ratio depletion and recovery to quantifiable levels) will be provided by dose level. PK/PD will be examined for association with AEs, pain scores and other endpoints, and changes in biomarkers.

Demographics and baseline status will be documented by dose level and/or overall, as applicable.

Descriptive statistics of change in pain score, analgesic use, peak expiratory flow, and shortness of breath will be collected by eDiary and/or during clinic visits. The Quality of Life (QoL) assessments will be collected at clinic visits and will be compared to pre-treatment screening run-in values. Trends in improvement or deterioration in these values with treatment and across the dose-level cohorts will be described.

Descriptive statistics of change from screening in serum and cellular biomarkers of inflammation, coagulation, and endothelial function will be provided.

ADAs will be described as present or absent and correlated with NKTT120 serum concentrations and iNKT cell recovery. Numbers of subjects with positive tests for ADAs per cohort and per study will be reported.

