- If 0 of 3 subjects in the cohort experiences a DLT, escalation to the next dose level cohort may proceed.
- If 1 of 3 subjects in the cohort experiences a DLT, 3 additional subjects will be added to the cohort.
- If  $\geq 2$  of 3 - 6 subjects experience a DLT, the MTD has been exceeded and dose escalation will cease. Three (3) subjects will be added to the previous lower dose cohort(s). The MTD is defined as the highest dose at which no more than one of six subjects experiences a DLT in the dose cohort.

A SRC will review all safety and laboratory data on all subjects in the study at regular intervals. The SRC will also be made aware of any adverse EOs that could be potential DLTs and any SAEs as soon as they are reported. Because of the complex nature of the disease, before any EO is determined to meet DLT criterion, the SRC will meet, ad hoc, to review the safety data for an individual before declaring the event is a DLT or not. While the SRC is determining if a DLT has occurred, no additional subjects will be enrolled.

The SRC will also assess safety signals that may become evident in the longer-term follow-up and will make recommendations to the Sponsor regarding study conduct and risk mitigation, as well as dose de-escalation protocol changes.

Note that peripheral iNKT cells will be followed as a pharmacodynamic marker of drug activity and that depletion of iNKT cells is an expected outcome and will not be considered a DLT. Acute pVOC and ACS or other SCD-associated AEs (e.g., hemolysis, hepatic/splenic sequestration, decreased haptoglobin, hemoglobinuria, bone pain, chest wall pain, pain in the extremity, priapism in men, gall stones, leg/ankle ulcers, avascular necrosis of bone, stroke, cognitive disabilities) will not automatically be considered DLT, but will be evaluated on a case-by-case basis and may be elevated to DLT status if warranted and related to NKTT120. This decision will be made by the SRC.

The primary endpoint (MTD or RDL) will be completed when the last subject dosed completes dosing plus two weeks of follow-up (time at which next cohort would have started). However, each subject will be followed until 1 month after their iNKT cells have returned to detectable levels. If the highest dose level is reached without determining a MTD, the RDL(s) for phase 2 will be determined by a dose that is at or below the highest dose and which is associated with iNKT cell recovery that allows dosing every 4-6 months in phase 2 studies.

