### Escalation scheme

Five dose levels of NKTT120 will be assessed. Each dose level will be administered as a single ascending IV dose. The dose levels to be investigated are 0.001, 0.003, 0.01, 0.03 and 0.1 mg/kg.

A standard dose escalation Fibonacci 3+3 design will be employed. Initially, three subjects will be treated. If no subject experiences DLT, dosing will escalate. If one subject experiences DLT, 3 additional subjects will be treated at the current dose and escalation will occur only if no more than 1 of 6 subjects experiences DLT. If  $\geq 2$  of 3 - 6 subjects experiences DLT at the initial dose level of 0.001 mg/kg, then it may be de-escalated. The study continues until MTD has been determined, or the highest dose cohort is filled. If no MTD is reached, RDL will be determined based on the overall safety profile of NKTT120 and the duration of iNKT cell depletion. The RDL(s) for phase 2 will be determined by a dose that is at or below the highest dose tested which is associated with timing of iNKT cell recovery that allows dosing every 4-6 months in phase 2 studies. The dose-level cohort that represents the RDL will be expanded to 6 subjects to confirm the RDL. [Table 5](#) below provides the probability of dose escalation.

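### Section 6.3.1 ties the MTD to a cohort with 2 of 6 DLTs, while Section 6.1 puts that same cohort above the MTD

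*Protocol*

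**What the plan says.** Four places in the Protocol bear on this.

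- **Section 6.3.1 (Primary Endpoint):** "The MTD is determined by a cohort in which 2 of 6 subjects experience a DLT". The same paragraph adds: "The dose-level cohort that represents the MTD will be expanded to 6 subjects to confirm MTD".
- **Section 6.1 (Overall Study Design):** if two or more of three to six "subjects experience a DLT, the MTD has been exceeded and dose escalation will cease". Three subjects are then added at the dose below. The definition follows: "The MTD is defined as the highest dose at which no more than one of six subjects experiences a DLT in the dose cohort".
- **Synopsis, Statistical methods:** the MTD is "defined as the dose level that is estimated to produce DLT in < 33% of subjects in a cohort using a 3+3 design".
- **Section 12, Escalation scheme:** after one DLT in the first three subjects and three more treated, "escalation will occur only if no more than 1 of 6 subjects experiences DLT". This passage governs escalation and does not define the MTD. It also gives the doses: "The dose levels to be investigated are 0.001, 0.003, 0.01, 0.03 and 0.1 mg/kg".

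**The concern.** The MTD is the primary endpoint of a first-in-human trial, and the rule that turns DLT counts into that endpoint should have one reading. Section 6.3.1, where a reader looks for it, links the MTD to the cohort outcome that Section 6.1 uses to declare the MTD exceeded. Two analysts who apply the two sections to the same data could report different doses. The confirmation step is unclear for the same reason: a 2-of-6 cohort already has six subjects, so expanding it to six would add nobody. At stake is which dose is reported as the MTD. When escalation stops is not in dispute.

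**Working it through.** **Inputs.** The MTD wordings are in Sections 6.3.1 and 6.1 and the synopsis. The escalation rule, doses and Table 5 are in Section 12. The true DLT rates below are illustrative, because the Protocol does not assume one.

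**Step 1: reproduce Table 5.** Escalation follows 0/3, or 1/3 then 0/3. With true DLT rate p:

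Pr(escalate) = (1−p)³ + 3p(1−p)² × (1−p)³

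At p = 0.30 this is 0.343 + 0.151 = 0.494, as printed. The rows from 0.05 to 0.80 all reproduce to three decimals. The last row, printed as 0.09 with 0.001, reproduces only if the rate is read as 0.90; at 0.09 the formula gives 0.922. That looks like a separate misprint and plays no part here.

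**Step 2: classify each outcome at which a cohort can end.**

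| Outcome | 6.3.1, literal | 6.1 | Synopsis | Section 12 |
|---|---|---|---|---|
| 0/3 | not addressed | not exceeded | 0%, accepted | escalate |
| 1/6 | not addressed | not exceeded | 16.7%, accepted | escalate |
| 2/6 | MTD | exceeded | 33.3%, rejected | no escalation |
| 2/3, 3/3, or 3 or more of 6 | not addressed | exceeded | 50% or more, rejected | no escalation |

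The synopsis and Section 6.1 sort every outcome the same way. The synopsis is only looser: it does not say the MTD is the highest such dose, and it does not mention six subjects. The conflict is in the 2/6 row, and Section 6.3.1 stands alone there.

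**Step 3: how often an escalating cohort ends at exactly 2/6.** This needs 1/3 followed by 1/3:

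Pr(2/6) = [3p(1−p)²]²

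The probability that the cohort stops escalation is 1 − Pr(escalate).

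| p | Pr(2/6) | Pr(stop) | Share of stops |
|---|---|---|---|
| 0.10 | 0.243² = 0.059 | 0.094 | 63% |
| 0.20 | 0.384² = 0.147 | 0.291 | 51% |
| 0.30 | 0.441² = 0.194 | 0.506 | 38% |
| 0.40 | 0.432² = 0.187 | 0.691 | 27% |

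The per-cohort probability peaks at 0.198, at p = 1/3.

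Across all five dose levels, the chance that escalation stops on exactly 2/6 depends on the assumed dose-toxicity curve. It is 0.12 for rates 0.02/0.03/0.05/0.08/0.10, 0.37 for 0.05/0.10/0.15/0.20/0.30, and 0.39 for 0.10/0.20/0.30/0.40/0.50.

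**Step 4: size of the difference.** The ratios of adjacent planned doses are 0.003/0.001 = 3.0, 0.01/0.003 = 3.33, 0.03/0.01 = 3.0 and 0.1/0.03 = 3.33. After 2/6 at a given dose, literal 6.3.1 reports that dose. Section 6.1 reports a lower one, by at least one level, since the lower cohort may itself fail when it is filled to six. After 2/6 at 0.001 mg/kg, no planned dose qualifies under Section 6.1, and Section 12 says de-escalation may follow.

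**The case against.** The best defence is that Section 6.3.1 describes a trigger: a 2-of-6 cohort stops escalation and so locates the MTD below it. The expansion sentence supports this, because expansion to six makes sense only for a cohort still at three, and Section 6.1 does add three subjects at the dose below. This carries weight. A reader might infer from 6.3.1 that a dose judged too toxic would be confirmed and carried forward; given the expansion sentence, the text does not support so firm a conclusion. But Section 6.3.1 does not state the trigger reading either. As a trigger it would also be incomplete, because it leaves out stops at 2/3, 3/3, or 3 or more of 6.

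Two other strong readings fail:

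- **Three incompatible definitions.** There are three wordings but two rules, because the synopsis limit sorts completed cohorts as Section 6.1 does.
- **Table 5 settles which definition was meant, or would need recomputing under the other.** Table 5 gives the probability of escalating. Escalation stops at 2/6 whether that cohort is labelled the MTD or above it, so the table is identical under both.

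It is also fair to say that the conflict bites only when a cohort ends at exactly 2/6. The fold-differences hold for the planned doses only, since Sections 6.1 and 6.6 allow a switch to smaller arithmetic steps.

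**Conclusion.** The point stands as an internal contradiction in the primary endpoint. Read literally, Section 6.3.1 makes a 2-of-6 cohort the MTD, while Section 6.1 and the synopsis exclude it. When that outcome occurs, the declared MTD differs by at least one level, 3.0- to 3.33-fold on the planned doses; at the starting dose, the choice is between that dose and no planned dose. The outcome is not a corner case: about 0.06 to 0.19 per cohort at assumed DLT rates of 0.10 to 0.30, and 38% to 63% of the cohorts that stop escalation at those rates. These probabilities assume independent subjects with a common DLT rate within a cohort. The contradiction itself does not depend on them. It must be fixed because it decides the primary endpoint and is cheap to remove.

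**What to change.** Reconcile Section 6.3.1, Section 6.1 and the synopsis into one MTD rule, expressed as a count of DLTs among a stated number of subjects and worded identically in all three places. Section 6.3.1 is the outlier. If its 2-of-6 outcome is meant only as the event that stops escalation, it should say so, cover the other stopping outcomes, and name the dose that is then reported. The same text should state which cohort is expanded to six to confirm the MTD, and what is reported if the stop occurs at the starting dose.

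The cost is a short text amendment. It needs no extra subjects and no new calculation: for this point the escalation rule in Section 12 and the Table 5 probabilities stay as they are.

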### **6.3.2. Secondary Endpoints**

#### **6.3.2.1. Pharmacokinetic (PK) Profile and Pharmacodynamic (PD) Endpoints**

Calculated PK parameters for NKTT120 will be determined, including  $C_{\max}$ ,  $C_{\text{avg}}$ , AUC,  $t_{1/2}$ , and  $V_d$ .

The PD endpoint consists of iNKT cell depletion and recovery after dosing with NKTT120. Recovery is defined as the detectable presence of iNKT cells.

#### **6.3.2.2. Biologic activity endpoints and biomarker activity**

The following endpoints will be used to determine the biologic activity of NKTT120:

- Changes in clinical measures of SCD activity, including changes from baseline in leukocyte counts, hemoglobin, reticulocytes (number and percentage of RBCs), platelet count, LDH, and CRP
- Change in pain frequency and intensity and use of analgesics compared to screening run-in from daily eDiary
- Changes in pulmonary function assessed at clinic visits as follows: forced vital capacity (FVC), forced expiratory volume in one second, forced expiratory flow rate at 25% to 75% of FVC (FEF25-75), peak expiratory flow rate, total lung capacity compared to screening run-in values

- 
- Changes in QoL domains defined by PROMIS short-form and ASCQ-Me domains, compared to screening run-in

The effect of iNKT cell depletion on biomarkers of inflammation, coagulation and endothelial activation will be explored by assessing changes from baseline in serum IFN $\gamma$ , TNF $\alpha$ , IL-1 $\beta$ , IL-6, IL-8, F1+2, D-dimers, vWF, sPLA2 and sP-selectin.

#### **6.3.2.2.1. Immunogenicity endpoint**

Immunogenicity of NKTT120 will be assessed by the presence or absence of anti-NKTT120 antibodies at EOS compared to baseline.

### **6.4. Number of Subjects**

Between 2 and 30 subjects are possible for enrollment under the 3+3 design.

### **6.5. Treatment Assignment**

There is no randomization in this trial. Eligible subjects will be enrolled into a phase I dose cohort determined by the time of their enrollment and the cohort that is still open for enrollment.

### **6.6. Dose Adjustment Criteria**

The lowest dose is based on the lowest dose of NKTT120 in the non-GLP cynomolgus monkey studies that resulted in 50% depletion of peripheral iNKT cells within 24 hours of dosing and their return to 80% of baseline by day four post-dosing. This dose represents the lowest pharmacologically active dose in cynomolgus monkeys. The highest proposed dose level (0.1 mg/kg,) is a dose level that might deplete iNKT cells in tissue for up to four months or longer; administering this dose to subjects would be contingent on the predicted exposure being less than that associated with the no adverse effect level (NOAEL) dose determined in the nonclinical GLP toxicology studies.

As the study progresses, the current dose escalation plan of approximately half log increment may be reduced to a slower arithmetic increment of dose escalation without increasing the number of maximum subjects if required due to information based on iNKT recovery times from the lower dose cohorts. Similarly, a dose de-escalation using 3+3 enrollment will be applied if indicated by the data and recommended by the Clinical Investigators and/or SRC.

#### **6.6.1. Safety Criteria for Adjustment or Stopping Doses**

DLT will be evaluated for each subject during the two-week interval following dosing. This interval will allow identification of any acute, dose-limiting events that will determine dose-escalation or expansion of dose-level cohorts. All EOI will be reviewed by the SRC to determine if they are a DLT.

Subjects who experience a DLT will remain in the study to complete the safety evaluations and follow-up until resolution or stabilization of the DLT. All AEs and SAEs will be determined and graded for intensity based on CTCAE criteria. AEs and SAEs will be determined to be

dose-limiting if they occur during the first two weeks post-dosing and meet the criteria described below.

All safety data, including adverse events and laboratory abnormalities, will be reviewed by the SRC periodically in order to assist the sponsor in evaluating potential safety signals during the follow-up until iNKT cells recover.

**Definition of DLT:** a DLT is defined only for adverse events that occur within 2 weeks of dosing (with the exception of any acute vaso-occlusive episode).

Any adverse event grade 3 or higher on NCI CTCAE version 4.03 will be considered an EOI and a potential dose limiting toxicity.

All adverse EOI below that could be dose-limiting toxicities will be reviewed immediately by the SRC to determine if they constitute a DLT. All serious adverse events at any time will be reviewed by the SRC so that the SRC can make recommendations to the Sponsor regarding dosing cohorts.

**Definition of EOI:** an EOI is defined only for adverse events that occur within 2 weeks of dosing (with the exception of any acute vaso-occlusive episode). Any adverse event grade 3 or higher on NCI CTCAE version 4.03 will be considered an EOI.

Additionally, the following study and disease-specific toxicities will be considered an EOI and evaluated to determine if a DLT has been experienced:

**iNKT cell-specific dose limiting toxicities:**

- Cytopenias. Defined as CTCAE version 4.0 grade 3 or 4 leukopenia, neutropenia, lymphopenia or thrombocytopenia. Specific grade 3 definitions in CTCAE version 4.03 are:
  - Leukopenia: <2000 cells/cubic milliliter
  - Neutropenia: <1000 cells/cubic milliliter
  - Lymphopenia: <500 cells/cubic milliliter
  - Thrombocytopenia: < 50/microliter
- Infections. Defined as CTCAE version 4.03 grade 3 or 4. Specific infections are detailed in the CTCAE. Broadly the definition is a severe infection that requires IV antibiotic, antifungal or antiviral therapy, or otherwise severe and medically significant, but not necessarily life-threatening.
- Cytokine storm syndrome. Defined as CTCAE version 4.03 grade 3 or 4. The grade 3 definition reads: Prolonged (eg, not rapidly responsive to symptomatic medication and/or brief interruption of infusion); recurrence of symptoms following initial improvement; hospitalization indicated for clinical sequelae (eg, renal impairment or pulmonary infiltrates)

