## **6. INVESTIGATIONAL PLAN**

### **6.1. Overall Study Design**

This is an open-label, multi-center, SAD Phase 1 study aimed at determining the MTD or RDL for Phase 2 of intravenously administered NKTT120 in adult subjects with stable SCD. For the purpose of this protocol, stable SCD is defined as not having experienced acute pVOC or ACS or other SCD-associated event requiring hospitalization or outpatient care within one month prior to dosing. In addition to determining the safety profile of NKTT120 in subjects with stable SCD, this study will also examine pain, analgesic use, QoL, pulmonary function, and inhaled SABA use. During the two-week screening run-in period and throughout the follow-up, subjects will keep a daily eDiary for pain, analgesic use, and inhaled SABA use. The ASCQ-Me and PROMIS QoL questionnaires will be administered at clinic visits. The screening run-in outcomes will be used as baseline comparison for values obtained post-dosing.

The study will evaluate single doses that are escalated over a range from 0.001 mg/kg to 0.1 mg/kg (0.001, 0.003, 0.01, 0.03, and 0.10 mg/kg). As the study progresses, the current dose escalation plan of approximately half log increment may be reduced to a slower arithmetic increment of dose escalation without increasing the number of maximum subjects if information about iNKT cell recovery times from the lower dose cohorts suggests it is necessary. Similarly, a dose de-escalation using 3+3 enrollment will be applied if indicated by the data and recommended by the Clinical Investigators and/or SRC.

Only one subject will be dosed per day and each subject will remain in the clinic for at least 6 hours after dosing for evaluation of any acute toxicity (i.e., infusion reactions, CRS, or allergic reactions) and for collection of post-dosing blood samples. Should CRS of any type be observed in subjects in any cohort, premedication with acetaminophen (1000 mg), histamine 2 (H2) receptor antagonists (diphenhydramine, 50 mg) and corticosteroids may be initiated prior to dosing of subsequent subjects to lessen the severity of CRS.

Dose escalation will be governed by a 3+3 design as follows:

- Dosing will begin at the lowest dose (minimally effective dose level), with 3 subjects per cohort.
- Each subject in the cohort must have completed at least two weeks of follow-up post-dosing before the first subject in the next cohort is dosed.

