#### **11.1.5. Laboratory Assessments**

Unexpected abnormal laboratory results will be defined as AEs and graded per CTCAE v. 4.03 criteria. All abnormal laboratory values will be reviewed by the investigator, who will determine clinical significance and relationship to NKTT120. Significantly out-of-range values will be flagged for rapid review by the investigator.

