##### **11.1.5.1. Hematology**

Hematology laboratory assessments will be performed at screening pre-run in, 6 hours post dose on Day 0, on day 14 and at each monthly follow-up visit, including the EOS visit. Hematology lab assessments include WBC, absolute and percent differential WBC, platelet count, RBC, hemoglobin, reticulocyte number and percent.

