### **11.4. Recording adverse events**

Adverse events spontaneously reported by the subject and/or in response to an open question from the study personnel or revealed by observation will be recorded during the study at the investigational site. Clinically significant changes in laboratory values, blood pressure, and pulse need not be reported as AEs. However, abnormal values that constitute an SAE must be reported and recorded as an AE. Information about pre-existing signs and symptoms will be collected from the time the subject signs an informed consent form. AEs will be collected from the first administration of study drug until the end of the study. SAE information will be collected from administration of study drug until their EOS visit, which is 30 days following the recovery of iNKT cells in the peripheral circulation. The AE term should be reported in standard medical

terminology when possible. For each AE, the investigator will evaluate and report the onset (date and time), resolution (date and time), intensity, causality, action taken, serious outcome (if applicable), and whether or not it caused the subject to discontinue the study.

Intensity will be assessed according to the CTCAE grading scale version 4.03.

It is important to distinguish between serious and severe AEs. Severity is a measure of intensity whereas seriousness is defined by the criteria in Section 11.2.1.2. An AE of severe intensity may not be considered serious.

In principle, pregnancy and the lactation period are exclusion criteria for clinical studies involving investigational drugs that are not directly related to the respective conditions. Should a pregnancy occur during this study, it must be reported and recorded on the pregnancy form and the subject should be followed in the study until one month after recovery of iNKT cells and during the entire course of the pregnancy and postpartum period. All recommendations described in the [Investigator Brochure](#) pertaining to pregnancy and lactation must be carefully considered. Pregnancy in itself is not regarded as an AE unless there is a suspicion that an investigational product may have interfered with the effectiveness of a contraceptive medication.

The outcome of all pregnancies (spontaneous miscarriage, elective termination, normal birth or congenital abnormality) must be followed up and documented even if the subject was discontinued from the study.

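### The printed cytopenia cut-offs, the adverse-event rule for laboratory values and the unnamed laboratory baseline leave the laboratory DLT criteria inconsistent

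*Protocol*

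**What the plan says.** **Cut-offs.** Section 6.6.1 lists cytopenias among the iNKT cell-specific dose-limiting toxicities, defines them by CTCAE grade 3 or 4, and then gives numbers said to be the CTCAE v4.03 grade 3 definitions. These include "Thrombocytopenia: < 50/microliter", "Neutropenia: <1000 cells/cubic milliliter" and "Leukopenia: <2000 cells/cubic milliliter", with lymphopenia in the same unit at 500. Section 11.1 repeats all four. Eligibility in Section 7.2 is stated in x 10^9/L: subjects are excluded with platelets at or below 150, neutrophils at or below 2, or lymphocytes below 1.0.

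**Adverse-event status.** Section 6.6.1 says "an EOI is defined only for adverse events that occur within 2 weeks of dosing", with an exception for acute vaso-occlusive episodes, and restricts DLTs in the same way. On laboratory values, Section 11.1.5 says "Unexpected abnormal laboratory results will be defined as AEs and graded per CTCAE v. 4.03 criteria". Section 11.4 says "Clinically significant changes in laboratory values, blood pressure, and pulse need not be reported as AEs", and adds that abnormal values constituting a serious adverse event must be recorded.

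**Baseline and timing.** The hemolysis criteria in Section 6.6.1 are a fall in hemoglobin from baseline (or to an absolute floor), or 3-fold rises from baseline in LDH, reticulocytes, AST or total bilirubin. Section 11.1.5.1 says "Hematology laboratory assessments will be performed at screening pre-run in, 6 hours post dose on Day 0, on day 14", then monthly and at end of study. Chemistry (11.1.5.2) and coagulation (11.1.5.4) follow the same times, and Table 3 agrees.

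**The concern.** The primary endpoint is the MTD or recommended dose level from a first-in-human 3+3 scheme, so it depends on counting DLTs in cohorts of three to six subjects. One DLT more or less in a cohort changes the decision. Cytopenia and hemolysis are criteria that come from laboratory data, and three links in their chain are loose: the number that flags the event, the rule that makes it an adverse event, and the sample or baseline against which it is judged.

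The printed platelet number and the Section 11.4 sentence both err towards fewer recognized DLTs and so towards escalation. The unnamed baseline can err either way: an old sample can create a false hemolysis flag as easily as hide a true one.

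**Working it through.** **1. Cut-offs against the protocol's own entry limits.** Conversions: 1 x 10^9/L = 1000 per microliter; 1 cubic millimeter = 1 microliter; 1 mL = 1000 microliters.

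| Line | Entry limit, per microliter | Printed cut-off | Comparison |
|---|---|---|---|
| Platelets | 150,000 | 50 per microliter | 150,000 / 50 = 3000-fold below |
| Neutrophils, read per cubic millimeter | 2000 | 1000 | 1000 / 2000 = one half |
| Neutrophils, read per mL | 2000 | 1 | 2000-fold below |
| Lymphocytes, read per cubic millimeter | 1000 | 500 | 500 / 1000 = one half |
| Lymphocytes, read per mL | 1000 | 0.5 | 2000-fold below |
| Leukocytes | none given | 2000 or 2 | no comparison possible |

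To meet the printed platelet figure, a subject at the entry limit would have to lose 1 - 50/150,000 = 99.97% of platelets. The platelet line uses a real unit, so no choice of unit rescues the number. The white-cell numbers are coherent under one reading and 1000-fold lower under the other.

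**2. Adverse-event status.** Take a non-serious grade 3 cytopenia on Day 14. Under Section 11.1.5 it is an adverse event if unexpected, is graded, and as grade 3 becomes an event of interest for the committee. Under Section 11.4 it need not be reported as an adverse event, so it need not become an event of interest. The general rule that any grade 3 or higher adverse event is an event of interest does not settle this, because it too requires an adverse event.

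**3. Sampling.** Hematology and chemistry fall at pre-run-in (4 weeks before dosing), 6 hours and Day 14. The unsampled stretch of the 14-day DLT window is 14 - 0.25 = 13.75 days, and 13.75 / 14 = 98%. Flow cytometry is drawn pre-dose, at 6 hours and on Days 1, 2, 7 and 14. It counts lymphocyte subsets only, not platelets, neutrophils, hemoglobin, LDH, AST or bilirubin.

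As an illustration only, suppose onset is uniform over 14 days and the abnormality lasts L days. The chance that it is present at a scheduled draw is (0.25 + L) / 14:
- L = 3: 3.25 / 14 = 23%
- L = 5: 5.25 / 14 = 38%
- L = 7: 7.25 / 14 = 52%

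With a Day 7 draw added, the figures become 45%, 73% and 100%.

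**4. Effect on the 3+3 scheme.** Table 5 follows from Pr(escalate) = (1 - p)^3 + 3p(1 - p)^5. At p = 0.30 this is 0.343 + 0.151 = 0.494, as printed. The nine rows from 0.05 to 0.80 reproduce; the last row, labeled 0.09, matches p = 0.90 (0.001) and not p = 0.09 (0.922).

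Table 5 presumes that every DLT is recognized. If only a share s is recognized, p is replaced by s x p. The documents give no value for s, so a range is shown:

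| True p | s = 1 | s = 0.75 | s = 0.5 | s = 0.25 |
|---|---|---|---|---|
| 0.30 | 0.494 | 0.654 | 0.814 | 0.944 |
| 0.40 | 0.309 | 0.494 | 0.709 | 0.906 |

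**The case against.** A reader might infer that laboratory DLTs cannot be called at all. The protocol does not support that. The CTCAE grade governs the cytopenia entry and the numbers are offered only as its transcription. The safety review committee adjudicates every event of interest and reviews all laboratory data periodically. Draws at 6 hours and Day 14 exist, and anything still present on Day 14 is sampled.

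Nor are all four cut-offs shown to be 1000-fold too low. The platelet number is clearly on the wrong scale; the white-cell lines may have only the unit word wrong. The CTCAE text is not in the protocol, so the exact correct figures must be taken from it.

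It is also too strong to say that laboratory changes are exempt from adverse-event reporting. Section 11.1.5 says the opposite and Section 11.4 keeps serious cases, so the defect is a contradiction.

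Finally, Section 6.1 says "The screening run-in outcomes will be used as baseline comparison for values obtained post-dosing", which could be read as fixing the laboratory baseline at a visit with no hematology or chemistry draw. That sentence closes a paragraph on diary and quality-of-life data. Section 6.3.2.2 compares pain, pulmonary function and quality of life with the run-in, but laboratory values with baseline. The laboratory baseline is therefore unnamed. By elimination it would be the pre-run-in sample.

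It is fair to add that Table 3 and Section 11.1.5 agree on draw times, so the sparse schedule is a design choice rather than an error, and that hemolysis is not automatically a DLT. What remains is a misprinted decision threshold in two sections, an undefined unit, two opposing rules on adverse-event status, and an unnamed baseline.

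**Conclusion.** The concern holds as a set of inconsistencies in the criteria that feed the 3+3 decision. The platelet cut-off is 3000-fold below the protocol's own entry limit and cannot express the grade it claims to transcribe. The white-cell unit is undefined. Sections 11.1.5 and 11.4 give opposite answers on non-serious laboratory abnormalities, and only adverse events can become DLTs. The laboratory baseline for hemolysis is not named, and the sole candidate is about 4 weeks old. These points rest on the text alone and should be corrected, because a site following the printed platelet number or Section 11.4 would misclassify events.

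The 13.75-day gap in hematology and chemistry is a fact of the schedule, with lymphocyte subsets the exception. Its consequence is less certain: the detection percentages depend on assumed onset and duration, and the escalation probabilities on an assumed recognition share. They show direction and possible size; they are not estimates for this trial.

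**What to change.** Three wording changes are needed:
- In Sections 6.6.1 and 11.1, reconcile the four cytopenia cut-offs with the CTCAE v4.03 grade already invoked, and state them in the eligibility units (x 10^9/L).
- Reconcile Section 11.4 with Section 11.1.5 so that any laboratory value meeting an event-of-interest criterion is recorded as an adverse event and goes to the safety review committee.
- Name the sample that serves as baseline for the laboratory DLT criteria.

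These cost only amendment text.

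Separately, the sponsor should consider adding hematology and chemistry at Day 0 pre-dose and Day 7, where blood is already drawn for flow cytometry, biomarkers and PK. That costs two routine laboratory sets per subject, at most 2 x 30 = 60 sets at the planned maximum, and a small extra blood volume. It would provide a baseline on the dosing day and break up the unsampled stretch. It is an improvement to weigh, not a correction of an error.
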